## 6.9. Protocol Adherence Criteria

Adherence to the protocol will be evaluated in several crucial aspects and will be categorized as high or low. Patients with low adherence to the protocol will be excluded from the sensitivity analysis by intention protocol but will be included in the analysis by intention to treat.

- **Patient withdrawal:** Low adherence will be considered when a patient voluntarily requests withdrawal of consent, experiences an adverse event unrelated to the study treatment, or is transferred to other medical facilities.

- **Non-compliance with the study protocol:** It will be classified as low adherence when a patient cannot receive 80% of the interventions required according to the protocol.

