| Comparator | Late multimodal therapy is defined as the initiation of multimodal therapy 3 days or more after the start of mechanical ventilation. The comparator differs from the study intervention only in the moment (time from orotracheal intubation to the start of multimodal therapy) of initiation of therapy.                                                                                                                                                                                                                                                                                                                                                                                                                                                                                                                                                                                                                                                                                                                                      |
| Outcomes   | 
Effectiveness
 
Primary outcome: Number of days with invasive mechanical ventilation in the ICU
 
Secondary outcomes:
 
 
• Days free of mechanical ventilation until day 28
 
• Days of delirium until day 28
 
• Time in ICU with delirium until day 28
 
• Days of hospitalization with delirium until day 28
 
• Sedation days until day 28
 
• Sedation-free days until day 28
 
• Barthel index at discharge
 
• Days of hospital stay
 
• Length of stay in ICU
 
• Mortality from any cause up to 90 days
 
• Time from intubation to start of therapy
 
• Muscle strength measured with the medical research scale council (MRC)
 
• Dysphagia at 72 hours
 
• Time until initiation of oral administration
 
• Development of healthcare-associated pneumonia,
 
• Maximum mobility measured by JH-HLM
 
• Grip strength
 
• Extubation failure
 
 |

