**Multidisciplinary Coordination:** Promoting collaboration among healthcare professionals, including doctors, nurses, therapists, and other specialists, to ensure comprehensive and personalized care.

**Communication with Family Members:** Maintaining clear and regular communication with the patient's family, providing information about the patient's condition, and offering emotional support.

**Crisis Management:** Being prepared to address emergencies and make quick and effective decisions in response to acute changes in the patient's condition.

Interventions will be performed daily once the patient has been included in the study and will be carried out according to the expert consensus recommending mobilization maneuvers when the patient has an FIO2 less than or equal to 0.6, a percutaneous oxygen saturation greater than or equal to 90%, a respiratory rate less than 30 breaths per minute, and a PEEP less than or equal to 10 cmH2O.

These maneuvers will be performed until the patient is discharged (defined as the moment when the intensivist determines that the patient can be transferred to hospitalization or discharged from the hospital) from the ICU.

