### 6.8 Losses and Handling of Missing data

- Frequency and Distribution: Losses during follow-up were recorded for participants in both study groups. Of [total number of participants] initially assigned, [number of participants lost] were lost during the study period.
- Reasons for Losses:
  - o Voluntary withdrawal of consent by the participant.
  - o Adverse events not related to the study treatment.
  - o Failure to comply with the study protocol.
  - o Transfer to other medical facilities.
- Comparison between Groups: A comparative analysis will be carried out between the control and intervention groups, to assess the equitable distribution of losses.
- Characteristics of Lost Participants: The baseline demographic and clinical characteristics of participants who completed the study will be compared with those who were lost to follow, to assess whether the losses introduced substantial biases.

- **Impact on Analysis:** A sensitivity analysis will be performed to evaluate the potential impact of losses on the study results. Results will be presented with both the inclusion and exclusion of missing participants.

- **Statistical Management:** In the main statistical analysis, the intention-to-treat approach will be used, including all participants according to their original assignment, regardless of their compliance or loss to follow-up. We will also perform a sensitivity analysis based on a per-protocol analysis since it could provide us with a measure of the effect of weaning under ideal treatment adherence conditions.

- **Replacement of Lost Participants:**

- o **Ethical Consideration:** Before considering the replacement of lost participants, an ethical evaluation of the justification for such action will be conducted. It will be considered whether the replacement is ethically acceptable and whether its implementation respects the rights and well-being of the participants.

- o **Imputation Methods:** If replacement of lost participants is considered, statistically sound and well-founded imputation methods will be used. Options such as imputation by the mean, LOCF, or other more advanced methods such as multiple imputation will be explored.

- o **Transparency and Documentation:** A detailed description of the imputation methods used will be provided, including the reasons for choosing a specific method. This will be included in the final reports and communication with the Ethics Committee.

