|                                          | maintain sustained attention, disorganization of thought, or fluctuating changes in level of consciousness).                   |                       | 4. Fluctuating changes in level of consciousness (+/-) |
| Days of delirium                         | Days with the presence of delirium                                                                                             | Discrete Quantitative | Days                                                   |
| Sedation days                            | Days with sedation                                                                                                             | Discrete Quantitative | Days                                                   |
| Sedation-free days                       | 28 days fewer days of sedation                                                                                                 | Discrete Quantitative | Days
It will be defined as 0 if the patient dies.   |
| Barthel index at hospital discharge      | The Barthel Index is a scale used to measure a person's degree of functional independence in activities of daily living (ADL). | Discrete Quantitative | It will be 0 if the patient dies.                      |
| Days of hospital stay                    | Days of hospital stay                                                                                                          | Discrete Quantitative | Days                                                   |
| Days of ICU stay                         | Days of ICU stay                                                                                                               | Discrete Quantitative | Days                                                   |
| Mortality                                | Death                                                                                                                          | Qualitative Nominal   | Yes or no                                              |
| Time from intubation to start of therapy | Time from intubation to start of therapy                                                                                       | Discrete Quantitative | Days                                                   |

Association between early multimodal therapy and days of mechanical ventilation in the intensive care unit of the Fundación Santa Fe de Bogotá: A randomized controlled clinical trial.

Version 6.0

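### The adherence rule that defines the per-protocol set has no start-time condition, although start time is all that separates the arms

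*Protocol*

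**What the plan says.** **The contrast.** The comparator row of the PICOT table in section 3 says "The comparator differs from the study intervention only in the moment" at which therapy begins. Section 6.5 agrees: the same type of maneuvers, by the same disciplines, within 24 hours of intubation in one arm and at 72 hours in the other.

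**The adherence rule.** Section 6.9 gives two routes to low adherence. The first is departure: "Low adherence will be considered when a patient voluntarily requests withdrawal of consent, experiences an adverse event unrelated to the study treatment", or is transferred elsewhere. The second is quantity: "It will be classified as low adherence when a patient cannot receive 80% of the interventions required according to the protocol". Neither mentions when therapy started.

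**Its use.** Section 6.9 continues: "Patients with low adherence to the protocol will be excluded from the sensitivity analysis by intention protocol". This is evidently the analysis announced in section 6.8: "We will also perform a sensitivity analysis based on a per-protocol analysis", justified there "since it could provide us with a measure of the effect of weaning under ideal treatment adherence conditions". Section 6.13 also plans a sensitivity analysis by protocol adherence.

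**The timing data.** The variable table in section 6.11 contains "Time from intubation to start of therapy", typed as a discrete quantity in days. Section 6.6 lists it among the exploratory outcomes. Nothing links it to the high/low adherence variable.

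**The concern.** A per-protocol set is meant to hold the patients who received what they were randomised to. Here the arms were randomised to a start time, and the content of therapy is the same in both. A rule that counts only how much therapy was delivered can therefore keep patients who did not receive their assigned timing.

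Such departures are plausible. Section 6.1 says that participants and researchers cannot be blinded, and section 6.5 describes the maneuvers as part of standard care in this unit. In Annex 1, respiratory therapy, physiotherapy and speech therapy start the late arm when the attending physician asks for a consultation, with no 72-hour minimum. The occupational therapy text, as printed, places both arms within the first 24 hours. A late-arm patient could start on day 1 in line with an annex and against section 6.5.

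At stake is the meaning of the per-protocol result. If it resembles the intention-to-treat result, a reader may take that as reassurance about adherence, although the set was never screened for the deviation that matters most in a timing trial.

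**Working it through.** The plan gives no figure to reproduce here, so the check applies the 80% rule as written.

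**Late arm, treated from day 1.** Required interventions are those due from 72 h to ICU discharge. Sessions given earlier are extra and cannot lower the share. If all due sessions are given, the share is 100%. For a 7-day stay, due days are 7 − 3 = 4 and the share is 4/4. For a 10-day stay it is 7/7. Length of stay does not matter: the early start is never penalised.

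**Early arm, first treated at 72 h.** Let D be the required therapy days, counted from when therapy was due, and m the days lost by the delay.

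- Share received = (D − m)/D. It reaches 80% when D = m/0.2.
- Assumption: m = 2 if days are due from 24 h, m = 3 if due from intubation; sessions fall evenly over days.

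| D | m = 2 | m = 3 |
|---|---|---|
| 6 | 4/6 = 67% | 3/6 = 50% |
| 10 | 8/10 = 80% | 7/10 = 70% |
| 15 | 13/15 = 87% | 12/15 = 80% |

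The thresholds are 2/0.2 = 10 and 3/0.2 = 15 days.

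**Weighting by Annex 1 session counts.** These are respiratory 3 per day, physical 2, speech 2, and occupational 1 under deep sedation, then 2. That makes 8 sessions on each lost day and 9 on each later day.

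- m = 2, D = 10: 72/(16 + 72) = 82%. At D = 9: 63/79 = 79.7%, which fails.
- m = 3, D = 14: 99/(24 + 99) = 80.5%. At D = 13: 90/114 = 78.9%, which fails.

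The thresholds become 10 and 14 days.

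**At the planning durations.** Section 6.3 uses mean ventilation of 3.4 and 6.1 days. ICU time after extubation is not given. Assume k further days, with therapy due from day 1 (so m = 2). The share for a 72 h start is (V + k − 3)/(V + k − 1).

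| k | V = 3.4 | V = 6.1 |
|---|---|---|
| 0 | 0.4/2.4 = 17% | 3.1/5.1 = 61% |
| 2 | 2.4/4.4 = 55% | 5.1/7.1 = 72% |
| 4 | 4.4/6.4 = 69% | 7.1/9.1 = 78% |

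All are below 80%. At typical planned stays the rule does catch this deviation in the early arm, though only indirectly, through lost sessions.

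**Alternative denominator.** Section 6.9 does not say from when required interventions are counted. If counting starts at the first session, an early-arm patient starting at 72 h can score 100% at any length of stay.

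**The case against.** The strongest reply is that an intervention required according to the protocol already implies its timing, and that detailed rules for a per-protocol set usually belong in an analysis plan not shown here. Section 6.2 also allows withdrawal of participants who do not follow the protocol, intention-to-treat is the main analysis, and start time will be reported by arm as an outcome. Part of this stands: the consequence is limited, and the early-arm example needs a long stay or the alternative denominator. But section 6.9 does not defer the definition. It states one, and that one has no timing test. Section 6.2 is permissive and does not mention start time. Annex 1 cannot supply the condition, because its late-arm start rules differ from section 6.5.

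Four stronger readings are tempting and are not supported.

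- **The 20% deviation limit in section 6.10 would miss timing crossover.** That limit refers to adequate compliance with the protocol and does not invoke the 80% rule. Timing violations could fall under it.
- **The section 6.5 criteria (FiO2, saturation, respiratory rate, PEEP) make the rule unfair to the early arm.** This requires sessions barred by the criteria to count as required, which the text leaves open, and all four disciplines to be withheld, whereas the criteria concern mobilization. Over 7 due days at 8 sessions per day, two barred days cost 4 sessions if only physical therapy stops (52/56 = 93%), or 6 if occupational therapy stops too (50/56 = 89%). Both still pass.
- **Start time cannot be verified because it is recorded in days.** The variable table says days, but the Annex 5 form gives no unit. The precision is unsettled; nothing shows that it is inadequate.
- **The treatment difference is diluted by a known amount.** The documents give no crossover rate, so no size can be stated.

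**Conclusion.** The point holds in limited form. As written, section 6.9 does not test the one feature that separates the arms. A late-arm patient treated before the late-arm start time stays in the per-protocol set at any length of stay, provided that at least 80% of the sessions later due are given. An early-arm patient first treated at 72 h stays in with about 10 to 15 or more required therapy days, or at any stay if counting starts at the first session. At the planning durations, with 0 to 4 assumed ICU days after extubation and counting from the due start, that patient would be excluded.

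The per-protocol analysis therefore does not reliably estimate the effect under ideal adherence to the randomised timing. The primary intention-to-treat result is untouched; the per-protocol analysis and the exploration by adherence are affected. The day thresholds rest on evenly spread sessions, or on the Annex 1 session counts, and on 2 to 3 lost days. The late-arm conclusion needs none of these assumptions.

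**What to change.** 1. Reconcile the late-arm start in section 6.5 with the start rules in the four Annex 1 therapy sections. Until then, a start-time condition has no single meaning for the late arm.
2. Add to section 6.9 an arm-specific start-time condition, taken from the protocol's own reconciled arm definitions, alongside the 80% rule.
3. State from when required interventions are counted, and whether sessions not permitted under the section 6.5 criteria count as required.
4. Record the first multimodal session by date and time, so that the condition can be checked.

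The cost is a few sentences and one date-time field, plus the reconciliation of Annex 1, which is needed in any case. The per-protocol set may become smaller.

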#### 6.10. Follow-up and Safety Procedures

- **Lack of Significant Difference in the Duration of Mechanical Ventilation:** If at the end of the study and after analysis of the data, there is no statistically significant difference in the mean duration of mechanical ventilation between the early therapy group and the late therapy group, the trial could be considered a failure in terms of demonstrating the effectiveness of early therapy in reducing days on mechanical ventilation.
- **High Rates of Protocol Deviation:** If more than 20% of participants in one or both groups do not adequately comply with the study protocol, this could affect the validity of the results and lead to trial failure.
- **Safety Concerns or Unacceptable Toxicity:** If an unexpectedly high rate of serious adverse events is observed in the early versus late therapy group, the trial could be considered a failure due to safety concerns.
- **Low Participant Recruitment or Retention Rate.**
- **External Interference or Changes in Clinical Practice:** If significant changes in standard clinical practice occur during the study that affect the interpretation of the results, the trial could be considered a failure. For example, if a new treatment or procedure is introduced that impacts the duration of mechanical ventilation regardless of the therapy assigned in the trial.

#### 6.11. Data Collection

**Variable description:**

| Variable                | Definition                           | Variable type           | Scale/Unit
measurement
categories
of
or  |
|--------------------------------|---------------------------------------------|--------------------------------|-----------------------------------------------------------------------|
| Age                            | Years old                                   | Quantitative

Discreet   | Years                                                                 |
| Weight                         | Weight                                      | Quantitative

Keep going | Weight in kilograms                                                   |
| Sex                            | Sex                                         | Qualitative
Nominal         | Female or male                                                        |
| Ethnicity                      | Ethnicity with which the patient identifies | Qualitative
Nominal         | Afro-Colombian

ROM

Indigenous

Raizal

None |
| Dialysis                       | Need for renal replacement therapy          | Binomial
Categorical        | 0: No

1: Yes                                                   |
| Norepinephrine support         | Need for norepinephrine support             | Binomial
Categorical        | 0: No

1: Yes                                                   |
| Maximum dose of norepinephrine | Dose in mcg/kg/min                          | Quantitative
continues      | Mcg /kg/min                                                           |
| Inotropic support              | Need for inotropic support                  | Binomial
Categorical        | 0: No

1: Yes                                                   |

|                             |                                                                                                                                                                                                         |                            |                                   |
|-----------------------------|---------------------------------------------------------------------------------------------------------------------------------------------------------------------------------------------------------|----------------------------|-----------------------------------|
| Vasopressin support         | Need for norepinephrine support                                                                                                                                                                         | Binomial Categorical       | 0: No
1: Yes                   |
| Vasopressin dosage          | Dose in IU/min                                                                                                                                                                                          | Quantitative continues     | IU/min                            |
| Barthel index               | The Barthel Index is a scale used to measure a person's degree of functional independence in activities of daily living (ADL).

Two RASS assessment points -3 or -2, RASS 0, and at ICU discharge | Discrete Quantitative      | It will be 0 if the patient dies. |
| body mass index             | It is the relationship between the patient's weight and height                                                                                                                                          | Quantitative
Keep going | Kilograms/Square meter            |
| Cluster                     | The group to which the patient was assigned                                                                                                                                                             | Qualitative Nominal        | 1: early
2: late               |
| Diagnosis                   | Principal diagnostic                                                                                                                                                                                    | Qualitative Nominal        | Diagnostic code CI10.             |
| Protocol Adherence          | Degree of adherence to the protocol                                                                                                                                                                     | Binomial Categorical       | 1: low
2: high                 |
| Type of respiratory failure | Development of hypoxemic ( $PaO_2 < 60$ mmHg) or hypercapnic ( $PCO_2 > 45$ mmHg) respiratory failure                                                                                                   | Binomial Categorical       | 1: hypoxemic
2: hypercapnic    |

|                                                                                  |                                                                                          |                            |                                                                                                            |
|----------------------------------------------------------------------------------|------------------------------------------------------------------------------------------|----------------------------|------------------------------------------------------------------------------------------------------------|
| Patient type                                                                     | Main pathology that led to the need for invasive mechanical ventilation.                 | Qualitative
Nominal     | 1 = surgical
2= neurological
3= septic/respiratory
4=cardiovascular
5=burned
6= respiratory |
| Sequential Organ Failure Assessment Score (COUCH)                                | System for evaluating the appearance and evolution of Multiorgan Failure in ICU patients | Discrete
Quantitative   | Number                                                                                                     |
| Acute Physiology and Chronic Health disease Classification System II (APACHE II) | Physiological classification of acute and chronic diseases                               | Discrete
Quantitative   | Number                                                                                                     |
| Simplified Acute Physiology Score II (SAPS II)                                   | disease severity assessment system                                                       | Discrete
Quantitative   | Number                                                                                                     |
| Tidal volume                                                                     | Amount of volume delivered with each breath                                              | Continuous
quantitative | Number                                                                                                     |
| Breathing frequency                                                              | Breathing frequency                                                                      | Discrete
Quantitative   | Number                                                                                                     |
| End expiratory pressure (PEEP)                                                   | End expiratory pressure (PEEP)                                                           | Continuous
quantitative | Number                                                                                                     |

|                                                                               |                                                                                      |                            |                    |
|-------------------------------------------------------------------------------|--------------------------------------------------------------------------------------|----------------------------|--------------------|
| Plateau pressure                                                              | Equivalent to alveolar pressure in the absence of flow                               | Quantitative
Continued. | Centimeters of H2O |
| Driving pressure                                                              | Driving pressure                                                                     | Continuous
Quantitative | Centimeters of H2O |
| Static compliance                                                             | Volume change divided by pressure change                                             | Continuous
Quantitative | ml/cmH2O           |
| Airway resistance                                                             | the resistance of the respiratory tract to airflow during inspiration and expiration | Continuous
Quantitative | Number             |
| Post-intubation PaO2/FIO2 index                                               | Pulmonary oxygenation and FIO2 relationship                                          | Continuous
Quantitative | Number             |
| Pneumotapponator pressure start IMV, start ventilatory assistance and weaning | Adjustment of pneumatic tamponade balloon to tracheal perfusion                      | Continuous
Quantitative | Centimeters of H2O |
| Delta POCC initiation of inspiratory effort and weaning                       | Non-voluntary inspiratory effort                                                     | Continuous
Quantitative | Centimeters of H2O |
| Muscle pressure in weaning (Pmus )                                            | Voluntary Force Magnitude                                                            | Continuous
Quantitative | Centimeters of H2O |
| P0.1                                                                          | Neural respiratory drive                                                             | Continuous
Quantitative | Centimeters of H2O |

|                                                |                                                                                                           |                            |                                                                                                                                                                                                                                            |
|------------------------------------------------|-----------------------------------------------------------------------------------------------------------|----------------------------|--------------------------------------------------------------------------------------------------------------------------------------------------------------------------------------------------------------------------------------------|
| Mobilization of secretions                     | Mobilization of secretions in the orotracheal tube                                                        | Qualitative
Nominal     | 
YES: Assessment by a respiratory therapist of the presence of abundant tracheobronchial secretions
 
NO: Subjective assessment by a respiratory therapist of the absence of abundant tracheobronchial secretions
 |
| Asynchrony index                               | Number of asynchronies witnessed in each time                                                             | Discrete
Quantitative   | Percentage                                                                                                                                                                                                                                 |
| NIF in weaning measured by respiratory therapy | Maximum negative inspiratory effort                                                                       | Quantitative
Continuous | Centimeters of H2O                                                                                                                                                                                                                         |
| NIF in weaning measured by physiotherapy       | Maximum negative inspiratory effort                                                                       | Quantitative
Continuous | Centimeters of H2O                                                                                                                                                                                                                         |
| % LEAK in weaning                              | % loss of tidal volume when deflating the pneumotaponator                                                 | Discrete
Quantitative   | Percentage                                                                                                                                                                                                                                 |
| Peak cough flow                                | Peak expiratory flow during a cough effort attempt                                                        | Continuous
Quantitative | maximum expiratory flow measurement in flow-time curve L/min                                                                                                                                                                               |
| Diaphragmatic excursion measurement            | It is the set of diaphragmatic forces combined with adequate intrathoracic and intra-abdominal pressures. | Continuous
Quantitative | Centimeters                                                                                                                                                                                                                                |

|                                                                    |                                                                                                                                                                                                   |                         |                                                                                                                                                                                                          |
|--------------------------------------------------------------------|---------------------------------------------------------------------------------------------------------------------------------------------------------------------------------------------------|-------------------------|----------------------------------------------------------------------------------------------------------------------------------------------------------------------------------------------------------|
| Diaphragmatic thickness % measurement                              | Diaphragm thickness                                                                                                                                                                               | Continuous Quantitative | $TF = (TEI - TEE) / TEE$
Millimeters                                                                                                                                                                  |
| Days necessary death                                               | Days necessary death                                                                                                                                                                              | Discrete Quantitative   | Number                                                                                                                                                                                                   |
| Days to start ventilatory support                                  | Days that were necessary from admission to the intensive care unit and the use of invasive mechanical ventilation                                                                                 | Discrete Quantitative   | Days                                                                                                                                                                                                     |
| Days from the start of ventilatory support to the start of weaning | Days from the start of ventilatory support (intubation) to the start of weaning                                                                                                                   | Discrete Quantitative   | Days                                                                                                                                                                                                     |
| Days of mechanical ventilation                                     | Days of invasive mechanical ventilation                                                                                                                                                           | Discrete Quantitative   | Days                                                                                                                                                                                                     |
| Days free of mechanical ventilation                                | 28 days minus ventilation days                                                                                                                                                                    | Discrete Quantitative   | Days

It will be defined as 0 if the patient dies or has been ventilated for more than 28 days.                                                                                                    |
| Delirium                                                           | For a patient to be considered to have delirium according to the CAM-ICU, both the first criterion (acute alteration in mental status) and at least one of the other three criteria (inability to | Qualitative Nominal     | 
 
1. Acute alteration of mental status (+/-).
 
2. Inability to maintain sustained attention (+/-).
 
3. Disorganization of thought (+/-).
 
 |

|                                          |                                                                                                                                |                       |                                                        |
|------------------------------------------|--------------------------------------------------------------------------------------------------------------------------------|-----------------------|--------------------------------------------------------|
